## 4. STUDY POPULATION

### 4.1 Population (base)

Patients with LA-HNSCC who are planned for cisplatin based primary concurrent CRT (as standard of care) in one of the participating centers of the Dutch Head and Neck Society will be asked to participate in this study. In the Netherlands yearly 250 LA-HNSCC are treated with primary CRT and in a previous study 54.5% patients had low SMM.

SMM will be estimated based on measurement of the cross-sectional area of the sternocleidomastoid muscle and paravertebral muscles on the level of the third cervical vertebrae (C3) on routinely performed CT or MRI. In patients who undergo FDG-PET/CT as part of the routine diagnostic work-up, as a control of SMM measurement at the level of C3, SMM will also be measured at the level of the third lumbar vertebra (L3), which is the most commonly used method in medical literature as a control of SMM measurement at the level of C3.

Seventy patients with low SMM will be randomised between low-dose weekly and high-dose three-weekly cisplatin therapeutic scheme with concurrent radiation. 59 patients with normal SMM will also be asked to participate in this study and will receive the standard of care of the centre they are admitted to (either three-weekly 100 mg/m^2 or weekly 40 mg/m^2 cisplatin). If 129 patients are included, but the minimum of 70 patients with low SMM is not yet reached, we will include additional patients until 70 patients with low SMM are included, in order to create sufficient power for statistical analysis. See paragraph 4.4 for the exact calculation.

### 4.2 Inclusion criteria

In order to be eligible to participate in this study, a subject must meet all of the following criteria:

- considered, eligible and planned for primary cisplatin CRT by treating physician;
- eighteen years of age or older;
- sufficient understanding of Dutch and medical consequences to give informed consent.

### 4.3 Exclusion criteria

A potential subject who meets any of the following criteria will be excluded from participation in this study:

- mentally disabled or patients with significantly altered mental status that would prohibit understanding and giving informed consent;
- a history of bilateral lymph node dissection in the neck and no available (PET-)CT scan of the third lumbar vertebra;
- an absolute contraindication for cisplatin as defined by the treating physician, including relevant pre-existing kidney insufficiency, clinically apparent vascular disease (for example

claudicatio intermittens), clinically relevant perceptible deafness, serious neuropathy and poor performance score;

- an absolute contraindication for high dose three-weekly cisplatin 100 mg/m^2 as defined by the treating physician;
- interval between diagnostic scan and planned CRT >2 months;
- cisplatin CRT planned as non-primary or induction treatment.

#### 4.4 Sample size calculation

In the retrospective study by Wendrich et al., out of 112 patients 30.4% experienced CDLT (meaning compliance to chemotherapy regimen was 69.6%). Using a cut-off 43.2 cm^2/m^2, 54.5% patients had low SMM. Patients with low SMM experienced CDLT more frequently than patients with normal SMM (44.3% vs. 13.7%,  $p < 0.001$ ). Thus compliance rates to chemotherapy regimen were 55.7% and 86.3%, respectively. We hypothesize therefore that in patients with low skeletal muscle mass and weekly low dose cisplatin, also 86.3% compliance will be reached. If we compare this compliance to an expected compliance of 55.7% in the arm of with a three-weekly high dose cisplatin, 33 patients with low SMM per arm are needed to show that the compliance in the weekly low dose cisplatin scheme is statistically significantly better than the threeweekly high dose scheme (two-sided alpha 0.05 and power 80%). With an expected drop-out of 5% 70 patients with low SMM are needed. Power calculations were done using PASS software. Since 54.5% of patients undergoing cisplatin based concurrent CRT have low SMM, to find the 70 patients with low SMM a total of 129 LA-HNSCC patients undergoing cisplatin based concurrent CRT are needed.

## 5. TREATMENT OF SUBJECTS

### 5.1 Investigational product/treatment

In this multicenter prospective randomised low intervention clinical trial patients with low SMM are randomised for three-weekly high dose (three cycles of 100mg/m^2) or weekly low dose (seven cycles of 40mg/m^2) cisplatin intravenously given with concurrent radiotherapy (35x 2 Gy; five times weekly with a total of 7 weeks). We consider both schemes as clinical equipoise, according to expert opinion. As previously mentioned, we aim to give a cumulative dose of more than 200 mg/m^2 and both schemes are used in daily clinical practice. All patients will be provided with supportive care according to local standard. Adequate pre- and posthydration, using sodium-chloride 0.9% solution with electrolyte suppletion will be performed. Furthermore, patients will receive anti-emetics, laxatives, diuretics and supportive care for treatment of side effects according to local standard. No experimental medications will be permitted while the patient is participating in this study.

### 5.2 Use of co-intervention

Co-interventions that might be used will be conform standard cisplatin based concurrent CRT protocol so therefore there will be no differences between the groups.

### 5.3 Escape medication

NA

## 6. INVESTIGATIONAL PRODUCT

For more detailed information regarding the investigational product (Cisplatin), we would like to refer to the attached SPC.

### 6.1 Name and description of investigational product(s)

Cisplatin in locally-advanced head and neck cancer consist of 100mg/m^2 every three weeks during three cycles, but the National Comprehensive Cancer Network guidelines mentions that dosing schedules of cisplatin other than three-weekly 100 mg/m^2 are also efficacious. According to the European Society of Medical Oncology guidelines, cisplatin is the preferred treatment for all patients with LA-HNSCC who are not fit enough for surgery or in whom functionality of the larynx should be preserved. Furthermore there is level II evidence for the efficacy of weekly 40 mg/m^2 cisplatin.

The intervention arm will receive 40 mg/m^2 cisplatin weekly during seven weeks. The control arm will receive 100 mg/m^2 cisplatin every three weeks for three cycles over a period of seven weeks. Administration is standardized for cisplatin and consists of intravenous cisplatin solution slowly (four hours) injected.

The combination of cisplatin with aluminium should be avoided, as stated by the Summary of Product Characteristics (See: Paragraph 6.2 on page 13). Preparation and labelling should be done conform hospital guidelines regarding chemotherapeutics. The standard procedures for chemotherapeutics should be followed. There is no need for the patient to return the medicine, because administration will take place in the hospital.

### 6.2 Summary of findings from non-clinical studies

Not applicable since cisplatin has been widely used in clinical practice over decades. It is registered in the Netherlands as a standard of care treatment (RVG 104068).

### 6.3 Summary of findings from clinical studies

Cisplatin is the preferred treatment for patients with unresectable LA-HNSCC or a functional larynx. The most common dosage is cisplatin 100mg/m^2 combined with 7 weeks of conventional radiotherapy, consisting of 70Gy in 35 fractions. Unfortunately high rates of severe acute and late adverse events remain of concern. Most common acute adverse events (AE) comprise of mucositis, dermatitis, emesis, anemia, leukopenia, thrombocytopenia and acute kidney injury. Late AE, compromising quality of life, consist of dysphagia, xerostomia, ototoxicity, radionecrosis and hypothyroidism.

To our knowledge three recent large randomized controlled trials compared cisplatin weekly low-dose to three-weekly high dose schemes. 1). Noronha et al. showed superiority of three-weekly high-dose cisplatin over weekly low-dose (30 mg/m^2) in the cumulative 2-year LRC (73.1% versus 58.5%) but a higher toxicity rate in the high-dose arm (84.6% versus 71.6%). No significant difference in compliance was found (p = 0.1). In this study relatively fit LA-HNSCC patients were included, which might cause

underestimation of incompliance to therapy in low SMM patients thus leading to a wrong conclusion in case of patients with low SMM. Also, the weekly treatment was underdosed (30 instead of 40 mg/m^2). Tsan et al. showed a higher compliance in the post-operative 100 mg/m^2 three-weekly cisplatin group compared to 40 mg/m^2 weekly cisplatin group. However, they do not report anything on skeletal muscle mass, performance status or body mass index. Thus, there might be a significant difference between baseline characteristics of the intervention and control group, contributing to the positive results in the three-weekly cisplatin group. Quon et al. showed that addition of very low-dose (20 mg/m^2) to RT did not improve survival. Despite lack of level I evidence, due to high toxicity rate, weekly low-dose cisplatin (40 or 30 mg/m^2) has substituted three-weekly cisplatin CRT in common practice and trials. This is in line with the recent National Comprehensive Cancer Network guidelines, which mentions that dosing schedules of cisplatin, other than three-weekly 100 mg/m^2 are efficacious. In an ongoing phase II/III study (JCOG1008), preliminary available results suggest that weekly 40mg/m^2 cisplatin post-operative is an appropriate and safe dose of cisplatin in high-risk patients improving OS, (local) relapse free survival and decreasing acute toxicities.

Thus weekly cisplatin (40mg/m^2) with concurrent RT, is commonly used in practice but not investigated in a large randomized controlled trial in patients with low skeletal muscle mass. As a level 2B category evidence, it is used anyway in practice.

#### **6.4 Summary of known and potential risks and benefits**

See explanatory text of chapter 6.1, 6.3 and the enclosed SPC.

#### **6.5 Description and justification of route of administration and dosage**

See explanatory text of chapter 6.1, 6.3 and the enclosed SPC.

#### **6.6 Dosages, dosage modifications and method of administration**

The intervention arm will receive 40 mg/m^2 cisplatin weekly during seven weeks. The control arm will receive 100 mg/m^2 cisplatin every three weeks for three cycles in the UMCU, Noordwest Ziekenhuisgroep, Leiden University Medical Center, and VUmc. Patient with a normal SMM in the AVL, will receive 40 mg/m^2 cisplatin weekly during seven weeks, since this is the standard treatment for the AVL. Administration is standardized for cisplatin and consists of intravenous cisplatin solution slowly (approximately four hours) injected.

#### **6.7 Preparation and labelling of Investigational Medicinal Product**

The investigational product has a marketing authorisation and is used in the authorised form for the authorised indication. Therefore, the investigational products are used from commercial stock and preparation and labelling are performed within the pharmacy department of the participating hospitals. No specific labelling is performed in this study. Administration will take place according to local guidelines and in line with recommendations in the National Comprehensive Cancer Network and European Society of Medical Oncology guidelines.

**6.8 Drug accountability**

Together with the local pharmacy, drug accountability according to the GCP guidance will be performed. The pharmacy will not label the IMP as explained in 6.7. Preparation for administration of cisplatin will be performed according to local standard pharmacy procedures. For each administration, patient-named drug accountability, as always done for chemotherapeutic agents, will be done, also according to local standard pharmacy procedures.

## **7. NON-INVESTIGATIONAL PRODUCT**

NA

## 8. METHODS

### 8.1 Study parameters/endpoints

#### 8.1.1 Main study parameter/endpoint

The primary outcome parameter is compliance (non CDLT) rate to the proposed cisplatin scheme. Compliance to chemotherapy is defined as the absence of CDLT. CDLT is defined as any toxicity resulting in a cisplatin dose-reduction of  $\geq 50\%$ , a postponement of treatment of  $\geq 4$  days or a definite termination of cisplatin after the first or second cycle of therapy. For weekly cisplatin regimens CDLT is defined as skipped cisplatin treatments or a definite termination of cisplatin before all scheduled cycles of therapy are given.

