
A retrospective study in patients with LA-HNSCC undergoing CRT with three-weekly cisplatin found an association between low skeletal muscle mass (SMM) and the occurrence of cisplatin dose limiting toxicity (CDLT). Total (whole body) SMM can reliably be estimated based on measurement of the cross-sectional area of the sternocleidomastoid muscle and paravertebral muscles on the level of the third cervical vertebrae (C3) on routinely performed CT or MRI. This method has been validated and appeared to be robust when comparing it to the common method measuring the muscle area at the level of the third lumbar vertebrae (L3). CDLT was defined as cisplatin induced toxicity causing either  $\geq 4$  days postponement of the treatment,  $\geq 50\%$  dose-reduction or termination of therapy before the third cycle. Patients with low SMM were more than three times more likely to develop CDLT compared to patients with normal SMM (44.3% vs. 13.7%); consequently, compliance (no CDLT) rate to planned chemotherapy scheme was 55.7% and 86.3%. Moreover, patients experiencing CDLT had

a lower overall survival than patients who did not (mean 36.6 vs. 54.2 months,  $p = 0.038$ ). Cisplatin possibly distributes mainly to the fat-free mass, of which SMM is the largest component, and thereby a higher and more toxic peak dosage might be reached in patients with low SMM receiving high dose cisplatin. Since early discontinuation of therapy automatically leads to a reduced cumulative cisplatin dose, which is associated with lower overall survival, it can be anticipated that particularly patients with low SMM might benefit from weekly low dose cisplatin based concurrent CRT to achieve an adequate cumulative dose comparable to patients with normal SMM. In this multicenter prospective randomised low intervention clinical trial, we aim to investigate if weekly low dose cisplatin can increase the compliance to the planned chemotherapy scheme in patients with low SMM to a level of compliance to three-weekly high dose cisplatin of patients without low SMM.

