### 10.2 Secondary study parameter(s)

Treatment toxicity is assessed with the Common Toxicity Criteria Adverse Events (CTCAE) v5.0 for a period of 24 months from the end of treatment. Toxicity scored as CDLT by the treating physician will be assessed, clarified if necessary, and reconfirmed separately. A severe toxic event is defined as a toxicity assessed as grade 3–5. Toxicities are classified as acute if they first appeared during or up to 3 months after treatment, and are classified as late if they persist, or first appear, more than 3 months after treatment. Multiple occurrences of events of a single toxicity type within an analysis time period are counted as a single event. Median numbers of toxicity events per patient (short-term [acute] toxicity and adverse long-term [late] effects, based on the TAME method of reporting toxicities) are compared between trial arms using t-tests. Proportions of patients affected by one or more toxicity event are compared between trial arms using Fishers exact test. Total administered cisplatin dose will also be recorded and means (or medians depending on the distribution) compared between trial arms.

Overall survival, disease-specific survival, loco-regional recurrences and time to recurrence are measured from the starting date of chemotherapy and compared between the three groups by the log-rank test with all-cause mortality in the intention-to treat population. Deaths are classified as being due to head and neck cancer or to other causes. Recurrences can be loco-regional or distant, or both. Patients who died from head and neck cancer causes as the first event are classed as recurrences. Patients on follow-up and patients lost to follow-up are censored at the last date at which they were known to be alive. Total time of follow-up per patient is two years. Hazard ratios and 95% CIs are generated with a univariate Cox proportional hazards model. The Schoenfeld residuals are tested by plotting the observed Kaplan- Meier values against the Cox predicted values. The effect of randomised treatment on outcome is also assessed after adjusting for known prognostic factors with a multivariate Cox proportional hazards model. At 3 months after treatment semi-structured interviews are conducted to obtain a better understanding of the patients' experience and preference for the treatment schemes, until saturation is reached. Semi-

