### 13.2 Synthesis

Chapter 13.1 is skipped, since cisplatin is indicated in HNSCC and will be administered in dosage schemes that are both common in clinical practice and acknowledged by the National Comprehensive Cancer Network and European Society of Medical Oncology guidelines. We would like to emphasize that both schemes can be considered as clinical equipoise according to expert opinion. In both schemes we aim to give a cumulative dose of more than 200 mg/m^2 since it has been proven that patients with locally advanced HNSCC have a survival benefit when receiving cisplatin above 200mg/m^2.

Assuming compliance in both arms is 100%, we do not expect differences in outcomes for both treatment groups. However, patients who are not able to fulfill the proposed treatment schedule have disadvantage in terms of overall survival. In a study by Wendrich et al. it was shown that people with low skeletal muscle mass had more often CDLT than people with a normal skeletal muscle mass (44.3% vs. 13.7%) and that patients with CDLT had a lower overall survival. Since we do not know whether patients with low skeletal muscle mass will tolerate a weekly scheme better than a three-weekly scheme, we are not yet able to conclude which scheme is superior. It could be that patients tolerate the weekly scheme better, which gives them a higher chance of receiving more than 200 mg/m^2 cisplatin and thus might improve survival rates. Regarding quality of life, it can also be that patients receiving the weekly scheme experience less cisplatin-related side-effects which might have a positive effect at quality of life. Still, there is no evidence available so the previous stated hypotheses can also be true for the three-weekly dose.

Due to the toxic side effects of cisplatin and the vulnerability of HNSCC patients, we do expect SAE and AEs to occur in both study arms. However this is in line with common standard of care and will not be related to the study procedure, which makes this study a low intervention clinical trial that does not need a DSMB or safety committee.

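### The primary endpoint (absence of CDLT) is worded differently for weekly cisplatin, so the two randomised arms are not scored by the same rule

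*Protocol*

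**What the plan says.** Protocol section 8.1.1 sets the endpoint: "Compliance to chemotherapy is defined as the absence of CDLT". It then gives two rules.

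- **General rule.** "CDLT is defined as any toxicity resulting in a cisplatin dose-reduction of" at least 50%, a postponement of at least 4 days, "or a definite termination of cisplatin after the first or second cycle of therapy". The termination limb names cycles that fit a three-cycle scheme.
- **Weekly rule.** "For weekly cisplatin regimens CDLT is defined as skipped cisplatin treatments or a definite termination of cisplatin before all scheduled cycles" have been given.

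Both rules feed the one primary outcome, which sections 2 and 10.1 compare between the randomised low-SMM arms on an intention-to-treat basis. Section 5.1 sets the schemes at three cycles of 100 mg/m² and seven cycles of 40 mg/m². Section 8.2 states that the trial is open label.

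Section 1 describes the retrospective three-weekly cohort behind the planning rates. Its CDLT definition was a postponement of at least 4 days, at least 50% "dose-reduction or termination of therapy before the third cycle". Section 4.4 takes 55.7% (low SMM) and 86.3% (normal SMM) from that cohort and sets the weekly arm at the higher figure: "We hypothesize therefore that in patients with low skeletal muscle mass and weekly low dose cisplatin, also 86.3% compliance will be reached".

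**The concern.** A randomised comparison of compliance measures the effect of the schedule only if both arms are scored alike. Here the weekly sentence omits two of the three types of event in the general rule, omits the causal phrase that ties events to toxicity, and adds a type of event (the skipped dose) that the general rule does not name. No section explains why the two rules should give comparable rates, and no common-definition analysis is planned.

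The protocol also leaves open whether the weekly sentence stands in place of the general rule or on top of it. The direction of the distortion depends on the answer, so neither a positive nor a negative primary result could be read cleanly as a difference in tolerance. The planning rate for the weekly arm inherits the same problem, because it was measured with the other rule.

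**Working it through.** **1. The two rules side by side (section 8.1.1)**

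| Event | General rule | Weekly sentence |
|---|---|---|
| Dose reduction of at least 50% | counts | not mentioned |
| Postponement of at least 4 days | counts | not mentioned |
| Skipped dose | not named | counts |
| Early termination | after cycle 1 or 2 | before all scheduled cycles |
| Caused by toxicity | stated | not stated |

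- *If the weekly sentence replaces the general rule*, reductions and delays count only in the three-weekly arm.
- *If it adds to the general rule*, reductions and delays count in both arms, and the weekly arm also carries the skip limb and is scored more strictly.

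The arms differ on both readings.

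**2. What this does to delivered dose (sections 5.1 and 8.1.1)**

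- Weekly, one full dose and six halved doses: 40 + 6 × 20 = 160 mg/m². Compliant on the replacing reading only.
- Weekly, one skipped dose: 6 × 40 = 240 mg/m². Non-compliant on either reading.
- Three-weekly, all doses given with one toxicity-related 4-day delay: 3 × 100 = 300 mg/m². Non-compliant.

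Section 13.2 states the dose aim: "In both schemes we aim to give a cumulative dose of more than 200 mg/m 2". The 160 mg/m² case misses it and the 240 and 300 mg/m² cases meet it, so scored compliance and that aim can disagree. These are boundary cases, chosen to show what the wording permits.

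**3. The plan's own sample size**

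Inputs from section 4.4: 55.7% and 86.3%, two-sided alpha 0.05, power 80%. The mean rate is (0.557 + 0.863)/2 = 0.710.

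n per arm = [1.960 × √(2 × 0.710 × 0.290) + 0.842 × √(0.557 × 0.443 + 0.863 × 0.137)]² / 0.306² = 33.3

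The stated 33 is reproduced to within rounding. Exact power of the uncorrected chi-square test at 33 per arm is 81.4%. Then 66/0.95 = 69.5, giving 70, and 70/0.545 = 128.4, giving 129. The arithmetic is sound; the question is what the 86.3% measures.

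**4. Replacing reading: false weekly benefit**

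Method: enumerate all 34 × 34 outcomes of two independent binomials with n = 33, and sum the probability of outcomes where the two-sided uncorrected chi-square gives p < 0.05 in favour of weekly. True tolerance is 55.7% in both arms. Let x be the share of weekly patients whose only event is a reduction or delay that the weekly sentence does not count. The documents do not give x, so the range is assumed.

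| x (points) | Scored weekly rate | Chance of a significant weekly benefit |
|---|---|---|
| 0 | 55.7% | 3.1% |
| 10 | 65.7% | 14.4% |
| 15 | 70.7% | 26.0% |
| 20 | 75.7% | 42.0% |

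**5. Either reading: loss of power from the skip limb**

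Same enumeration, three-weekly arm at 55.7%, with the weekly rate lowered from 86.3% by an assumed loss.

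| Loss (points) | Scored weekly rate | Power |
|---|---|---|
| 0 | 86.3% | 81.4% |
| 10 | 76.3% | 44.1% |
| 15 | 71.3% | 27.7% |

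If unrelated skips were scored as CDLT, an assumed 1% to 3% per cycle would be enough to move the rate this far. The scored rate would be 0.863 × 0.99⁷ = 80.4% to 0.863 × 0.97⁷ = 69.7%, and power 60% to 23%.

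**The case against.** The strongest reply is that the general sentence is not limited to three-weekly treatment, so the weekly sentence may simply add to it. Reductions and delays would then count in both arms, and the 160 mg/m² example and the false-benefit table would fall away. That is a fair reading, and the text does not exclude it. What stands is that the weekly arm would then be scored more strictly than the other.

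Some tailoring is unavoidable, since a limb naming cycles 1 and 2 cannot serve seven cycles, and a skip covers part of what a delay limb would catch. That explains the termination wording. It does not explain the absence of the reduction limb.

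The 86.3% is presented as a hypothesis, set at the level of normal-SMM patients. Section 1 also cites a review with 88% adherence on weekly and 71% on three-weekly cisplatin, but the protocol does not give that review's definition of adherence, so the support is partial.

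Four stronger readings are tempting, and the protocol does not support them:

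- *Non-toxic skips, or never starting, definitely count against weekly.* CDLT stands for cisplatin dose limiting toxicity, so the missing causal phrase is a gap in wording. It does not show that cause is irrelevant in that arm. Patients who never start are plainly covered by neither rule.
- *CDLTs that the physician misses are never found.* Section 10.2 says "Toxicity scored as CDLT by the treating physician will be assessed, clarified if necessary, and reconfirmed separately", but section 8.3 also has the investigator collect CDLT, toxicity and changes of treatment for each week.
- *No analysis could repair this.* A common rule could be derived if the dose and date records are adequate.
- *Nothing arm-neutral is planned.* Cumulative cisplatin dose is already a secondary comparison (sections 8.1.2 and 10.2), although it does not repair the primary test.

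**Conclusion.** The concern holds as a defect in the definition of the primary endpoint. The randomised arms are scored on different types of event, the protocol does not say how the two rules relate, and the 86.3% does not directly estimate the endpoint that will be scored in the weekly arm.

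The direction of bias cannot be settled from the protocol. If the weekly sentence replaces the general rule, the missing limbs favour weekly while the skip limb works against it. If it adds, the difference works against weekly. The sizes calculated above are illustrations: they rest on assumed shifts of 10 to 20 points, on 33 evaluable patients per arm and on an uncorrected chi-square test, and the false-benefit series applies only to the replacing reading. They show that moderate shifts matter at this sample size. They do not show that such shifts will occur. The point should be settled before the primary analysis because it decides what the single primary comparison means.

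**What to change.** 1. Reconcile the two sentences of section 8.1.1 so that both arms are scored on the same types of event, with the same toxicity requirement and the same handling of randomised patients who never start. State whether the weekly sentence replaces or adds to the general rule. The thresholds are for the sponsor to settle.
2. Derive the endpoint by program for every randomised patient from the administration records (section 6.8) and the weekly CDLT and toxicity data (section 8.3), after confirming that dose and date are captured for each administration.
3. If two rules are kept, justify them and pre-specify a common-definition analysis of the primary comparison. Support it with percent of planned cumulative dose (300 against 7 × 40 = 280 mg/m²) and the proportion above the protocol's own 200 mg/m² aim, building on the existing cumulative-dose secondary endpoint.
4. Re-justify the 86.3% in section 4.4 under the rule that will score the weekly arm.

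The cost is amendment wording and a derivation program, with no extra study procedures. The drawback is that the expected weekly rate may prove less favourable than 86.3%, in which case 33 per arm would no longer give the planned power.
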